### Recruitment

All Dutch- and French-speaking family physicians who use HealthOne in their daily practice will be informed about the study and will be sent an e-mail invitation to participate by one of the researchers. Physicians who do not react to the e-mail after 14 days will be sent a reminder. Any physicians who do not react to the second reminder will be telephoned by one of the researchers after another seven days.

### Randomization

Physician practices that agree to participate will be randomly assigned to one of the two groups following simple randomization procedures. Randomization will be performed by a statistical consultant with an electronic random list generator, anonymously for the researchers. Allocation will be concealed from the participants until the study start and after physicians’ informed consent is obtained. Physicians will be aware of the allocated arm; patients will not be informed about the intervention. Data analysts will be kept blinded to the allocation. Outcomes are objective measures directly extracted from the electronic medical records.

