## Methods

The study is a cluster-randomized trial with before/after measurements conducted in Belgian family medicine. A cluster design is necessary to minimize contamination that might occur if individual patients were randomized. Randomization will be performed at practice level; the intervention will happen at physician level; and data will be analyzed at patient level, in a multilevel analytical approach. The follow-up period of the study will be 12 months.

Physicians’ practices will be randomly assigned to the intervention or control group in a 1:1 ratio, to receive either the EBMeDS reminders or to follow the usual care process.

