### Participants and setting

Physicians eligible to participate in the study are all family physicians (739 Dutch-speaking and 891 French-speaking) using HealthOne (1,630 family physicians). Physicians will be included if the following criteria are met:

1. The physician has integrated HealthOne in his consultations;

2. The physician uses the functionality of e-prescribing within HealthOne so that prescribed medication can be identified from the electronic medical records; and

3. The physician agrees to be involved in the study.

Patients are included if:

1. They are 18 years or older.

2. They have their electronic medical records registered with one of the participating family physicians. Medical records are not centralized in Belgium. Patients are free to choose any physician, and can even see several physicians at the same time. To encourage a patient to have their medical records held by a single physician, a voluntary enlisting program was introduced (Global Medical File) a decade ago. For every enlisted patient, the general practitioner who keeps their central medical records receives a registration fee. Enlisted patients are reimbursed to a larger extent by the health insurance fund.

3. They are enlisted and have an established diagnosis of diabetes at the baseline time point of the study (identified as having: an ICPC code of diabetes; or a prescription for a diabetes-specific drug; or the necessary laboratory results to confirm diabetes).

Exclusion criteria are pregnancy and cognitive impairment.

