### Outcomes

#### Baseline measurements

Baseline demographic data on patient age, gender, years since the diagnosis of diabetes, nursing home residence (yes/no), HbA1c, cholesterol levels, and blood pressure will be collected. Data on physician age, gender, years of experience, and native language will be requested as well.

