### Sample size

Based on the data in the literature, a mean difference of 0.3% in HbA1c change could be considered clinically significant (SD of HbA1c change 1.3%) [23-25]. To detect a mean difference of 0.3% in HbA1c change at four post-treatment occasions, with a two-sided unpaired *t*-test, a 5% family-wise significance level and Bonferroni correction for multiple testing, 1:1 allocation and a power of 80%, a sample size of 463 patients in each group will be necessary, assuming a withdrawal rate of 10%. Additional adjustment for clustering of patients within physician practices by the design effect [26], assuming 10 patients per cluster and an intra-class correlation coefficient of 0.047 based on data in the literature [27], leads to a sample size of 659 patients in each arm. Sample size calculations were based on historical data. They can be adjusted after baseline registrations if correct standard deviations and intra-cluster correlation coefficients are known. Sample size calculation was performed using SAS software.

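### Simple randomization of practices is valid, but it gives 1:1 only in expectation and leaves language balance to chance; blocks stratified by language would be a cheap improvement

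*Protocol article*

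**What the plan says.** The Methods section says practices are "randomly assigned to the intervention or control group in a 1:1 ratio", and the abstract says the same. It also defines the levels of the design: "Randomization will be performed at practice level; the intervention will happen at physician level; and data will be analyzed at patient level". The Randomization section gives the mechanism: "Physician practices that agree to participate will be randomly assigned to one of the two groups following simple randomization procedures". A statistical consultant runs an electronic list generator, and no restriction on the list is described.

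On language, Participants and setting describes the eligible pool as "all family physicians (739 Dutch-speaking and 891 French-speaking) using HealthOne (1,630 family physicians"). Baseline measurements adds: "Data on physician age, gender, years of experience, and native language will be requested as well".

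On practice size, the only figure is in Sample size: "assuming 10 patients per cluster and an intra-class correlation coefficient of 0.047 based on data in the literature". Data collection puts the first extraction before the study starts but does not say whether it comes before or after randomization.

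On imbalance, Data analysis compares the arms at baseline and adds variables to the model only where it finds differences it regards as important. It names no variable and no threshold.

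**The concern.** The randomized unit is the practice, so the number of independent allocations is far smaller than the number of patients. Simple randomization leaves both the split of practices and the language mix of the arms to chance. Language is identified before recruitment, so it could be balanced by design. The allocation method is stated outright, and it has to be settled before the trial starts; a later analysis plan cannot change it.

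What is at stake is some precision and the clarity of the primary model. If the arms differ by language, the only remedy in the text is an adjustment prompted by observed differences, so whether language is in the model depends on the data.

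**Working it through.** **Inputs from the protocol article.** HbA1c difference 0.3%, SD of change 1.3%, two-sided 5% with Bonferroni over four occasions (0.05/4 = 0.0125 per test), power 80%, withdrawal 10%, 10 patients per cluster, ICC 0.047; 739 Dutch-speaking and 891 French-speaking physicians.

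**Step 1: the plan's own sample size.** Per arm, n = 2 × 1.3² × (2.498 + 0.842)² / 0.3² ≈ 419. With 10% withdrawal this becomes 461 (× 1.1) or 466 (÷ 0.9). The exact t-test needs 421, which gives 464 or 468. The stated 463 is reproduced within rounding and method. The design effect is 1 + 9 × 0.047 = 1.423, and 463 × 1.423 = 658.8, so 659. The sample size is not in dispute.

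**Step 2: number of practices.** 659/10 rounds up to 66 per arm, or 132 in total. The document does not state this number.

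**Step 3: split of practices.** Under simple randomization the number in one arm is Binomial(132, 0.5).
- P(exactly 66:66) = 6.9%.
- 95% range for one arm: 55 to 77.
- P(76:56 or worse) = 9.8%.

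**Step 4: what an uneven split costs.** Patients analysed per arm = practices × 10 × 0.9. SE = 1.3 × √[1.423 × (1/n₁ + 1/n₂)], and power = Φ(0.3/SE − 2.498).

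| Split | n₁, n₂ | SE | Power |
|---|---|---|---|
| 66:66 | 594, 594 | 0.0900 | 79.8% |
| 56:76 | 504, 684 | 0.0910 | 78.7% |
| 55:77 | 495, 693 | 0.0913 | 78.5% |

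Averaged over all possible splits, power is 79.5%. Forcing 1:1 therefore gains about 0.4 points on average.

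**Step 5: language.** Assume participating practices mirror the physician split and are each of one language: 891/1,630 = 54.7%, so 72 French-speaking and 60 Dutch-speaking practices. With independent Binomial(72, 0.5) and Binomial(60, 0.5) draws, the between-arm difference in language share has an SD of 8.7 points. P(more than 10 points) is 24.7%, and P(more than 15 points) is 8.5%.

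**Step 6: how much a language gap could matter.** Take the planning ICC to apply to HbA1c change. Between-practice variance is then 0.047 × 1.3² = 0.0794. If language explained all of it (an implausible upper limit), the two groups would differ by √[0.0794/(0.453 × 0.547)] = 0.57%, and a 10-point gap would move the estimate by about 0.06%. If language explained 20% of it, the shift would be about 0.025%. The planned SE is 0.09% and the target difference 0.3%.

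**The case against.** The strongest reply is that nothing is wrong. Simple randomization is unbiased, and with about 132 units large imbalances are uncommon. Chance differences by language are part of the between-practice variation that the design effect and the practice random intercept already cover. That stands.

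A reader might infer four stronger claims, and the documents do not support them:
- **That the method contradicts the 1:1 ratio.** A 1:1 ratio is normally read as equal allocation probability, and simple randomization delivers that. No exact split is promised.
- **That practice size is also known beforehand.** The article only assumes 10 patients per cluster. The first extraction is not ordered relative to randomization. It also needs each physician's confirmation and passes through an independent person who alone holds the link to physician identity. A count tied to a named practice before allocation would be an additional step.
- **That precision suffers materially.** Step 4 shows about 1 point of power at 76:56.
- **That language is a known prognostic factor.** No section says HbA1c change differs between the language groups.

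It is also fair to say that adjustment prompted by observed differences is a separate weakness of the analysis. Stratification resolves it only for the stratification factor.

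**Conclusion.** The point holds as a modest improvement. Practices are allocated without restriction although language is documented before recruitment, so its balance is left to chance without need. The cost of an uneven split is small: a 9.8% chance of 76:56 or worse, with power at 78.7% instead of 79.8% when the split is 76:56. The chance of a language gap above 10 points is about one in four, but its effect on the estimate is probably well below one standard error, and the inference remains valid.

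These figures rest on the derived 132 practices, on practices mirroring the physician language split, and on the planning ICC and SD. Fewer, larger practices would make imbalance more likely: with 60 practices the chance of a language gap above 10 points is about 43%. The main gain is balance on language and a language adjustment fixed in advance.

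**What to change.** In the Randomization section, replace simple randomization with permuted blocks of consented practices, stratified by language (Dutch or French), with the list prepared by the same statistical consultant. In the Data analysis section, state that language enters the primary linear mixed model as a prespecified fixed effect whether or not imbalance is observed.

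Add practice size as a second stratum only if a count of eligible patients per practice is obtained before allocation. If it is not, stratify by language alone.

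The cost is a slightly more complex random list and one extra model term, with no additional patients. Language must be recorded for each practice at consent, with a rule for any practice that works in both languages.

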### Data analysis

Descriptive statistics will be provided regarding baseline variables of the patients and the family physicians. Intervention and control groups will be compared regarding baseline variables to evaluate the randomization. Linear mixed models will be used for continuous patient-level variables, with a random intercept to account for clustering of patients within physician practices. Logistic regression models based on generalized estimating equations (GEE) to account for clustering will be used for binary patient-level variables.

Differences between intervention and control groups regarding continuous outcome measures (change versus baseline in HbA1c, cholesterol levels, and blood pressure) will be assessed using linear mixed models (multilevel regression models) with random intercepts for physician practices and random intercepts for patients to account for repeated measurements over time. The primary fixed effect of interest will be the difference between intervention and control group, which will be tested at each time point (3 m, 6 m, 9 m and 12 m). If important differences in baseline characteristics are demonstrated between both groups, we will account for that by including the relevant variables in the model.

Differences between intervention and control groups regarding three-level composite scores (worsening, unchanged, improvement) will be assessed using random-effects proportional odds models, or, in case the proportional odds assumptions do not hold, baseline-category logits models, with random intercepts for physician practices and random intercepts for patients to account for repeated measurements over time. As with the analysis of continuous outcomes, differences between intervention and control groups will be tested at all time-points, and correction for imbalance in baseline characteristics will be applied if indicated.

To study the effect of the actual use of the EBMeDS system on the outcome measures, models similar to those described above will be used for analyzing the effect of intervention. However, they will now include a measure for the use of EBMeDS as the main explanatory variable, and will restrict analysis to the data obtained in the intervention group.

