### Primary and secondary outcomes

Primary outcome is the one-year pre- to post-implementation change in HbA1c.

Secondary outcomes are the one-year differences in cholesterol levels and systolic and diastolic blood pressure. A composite patient score and a composite process score are calculated representing the change in diabetes (process) control and associated cardiovascular risk [19]. The composite patient score consists of reaching the evidence-based targets for glycated hemoglobin, blood pressure (systolic and diastolic), and cholesterol. The process composite score consists of meeting the evidence-based targets of the number of blood pressure measurements, the number of laboratory results of HbA1c, cholesterol and micro-albuminuria, a prescription of statin (yes/no), if high cardiovascular risk a prescription of aspirin/clopidogrel (yes/no), if hypertension or nephropathy ACE inhibition/sartan (yes/no).

Outcomes that cannot be reliably detected from the electronic medical records such as smoking status, and feet and eye examinations are excluded from the composite scores, as well as outcomes in which family physicians’ influences are minimal (*e*.*g*., BMI, physical activity, etc.).

Outcomes of the composite scores with their respective targets are shown in Table 1. Recommendations and targets are based on the diabetes guidelines of Domus Medica [20] and the Belgian ‘Zorgtraject diabetes’ [21].

**Table 1 T1:** Variables included in the composite scores

***Variable***	***Process target***	***Maximum score per period****	***Clinical target***	***Maximum score per period***^**†**^
HbA1c	Quarterly	2	< 7%	1
Blood pressure	Quarterly	2	< 130/80 mm Hg	1
Cholesterol (LDL, HDL, Total)	Annual	1	LDL < 100 mg/dL	1
Microalbuminuria check	Annual	1		
A prescription of statin	Yes/no	1		
If high cardiovascular risk, a prescription of aspirin/clopidogrel	Yes/no	1		
If hypertension or nephropathy, ACE inhibition/sartan	Yes/no	1		
Total		9		3

*Maximum score for process composite per period = 9 (7 variables).

^†^ Maximum score for patient composite per period = 3 (3 variables).

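### Random intercepts alone give all four HbA1c changes one variance, so the 12-month standard error will be too small if the variance of change rises over follow-up

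*Protocol article*

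**What the plan says.** The primary endpoint is a one-year quantity (protocol article, Primary and secondary outcomes): "Primary outcome is the one-year pre- to post-implementation change in HbA1c".

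The Data analysis section takes as its response "continuous outcome measures (change versus baseline in HbA1c, cholesterol levels, and blood pressure") and fits linear mixed models "with random intercepts for physician practices and random intercepts for patients to account for repeated measurements over time". The effect of interest is the difference between arms, "which will be tested at each time point (3 m, 6 m, 9 m and 12 m"). That section names no visit-specific variance, random slope, practice-by-visit effect or robust standard error.

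The Sample size section plans a "two-sided unpaired" t-test with "a 5% family-wise significance level and Bonferroni correction for multiple testing, 1:1 allocation and a power of 80"%. It gives a single standard deviation of change, 1.3%, for all four occasions. No standard deviation by visit and no correlation between visits appears anywhere in the article.

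**The concern.** A patient intercept plus a practice intercept, with independent residuals of constant variance, implies that the change at 3 months is as variable as the change at 12 months. It also implies that any two visits are equally correlated and that a practice's effect is the same all year.

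Every response here is a difference from the same baseline value. If the HbA1c variance itself is stable, the variance of change at visit t is 2σ²(1 − ρ_t), where ρ_t is the correlation with baseline. Repeated measurements usually correlate less as the gap widens, so a rising variance is the natural expectation.

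The model would then spread the variance evenly over the visits. The 12-month contrast would get a standard error that is too small, and the 3-month contrast one that is too large. At stake is the confidence interval and p-value for the primary endpoint.

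**Working it through.** **1. The plan's own figures.** Inputs (Sample size): difference 0.3%, SD of change 1.3%, two-sided level 0.05/4 = 0.0125, power 80%, withdrawal 10%, 10 patients per cluster, intra-class correlation 0.047.
- Exact t-test: 421 per arm. Then 421 × 1.1 = 463.1, the stated 463.
- Design effect: 1 + 9 × 0.047 = 1.423. Then 463 × 1.423 = 658.8, the stated 659.

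Both figures reproduce, and this point does not touch them.

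**2. What the model does to the 12-month standard error.** With complete data and arm-by-visit terms, the estimated 12-month effect is the difference in 12-month means. Its model-based standard error uses the variance averaged over the four visits. Hence:
- model SE / true SE at visit t = √(mean variance / variance at t);
- actual type I error = 2 × [1 − Φ(z × that ratio)], with z = 2.498 for a level of 1.25%.

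This takes the variance pattern to be the same at patient and practice level.

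**3. Main illustration (assumed correlations with baseline 0.80, 0.70, 0.62, 0.55).**
- 1 − ρ_t = 0.20, 0.30, 0.38, 0.45; mean = 1.33/4 = 0.3325.
- 12-month variance relative to the mean: 0.45/0.3325 = 1.35.
- 12-month SE ratio: √(0.3325/0.45) = 0.86, so the standard error is 14% too small.
- Type I error at 12 months: 2.498 × 0.860 = 2.147, which gives 3.2% against the planned 1.25%.
- An ordinary 95% interval would miss 9.2% of the time (1.960 × 0.860 = 1.685), so its coverage would be 90.8%.
- 3-month SE ratio: √(0.3325/0.20) = 1.29, so the early test is conservative.

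In HbA1c units, if the 12-month SD is 1.3%, the true standard error is 1.3 × √(2 × 1.423/659) = 0.085. The model would report 0.085 × 0.86 = 0.073.

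**4. How much the answer depends on the assumption.**

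| Assumed pattern | 12-month SE ratio | Actual level of the 1.25% test |
|---|---|---|
| Constant SD, stable practice effects | 1.00 | 1.25% |
| Correlation with baseline 0.60 falling linearly to 0.50 | √(0.45/0.50) = 0.95 | 1.8% |
| SDs 1.0, 1.1, 1.2, 1.3 | 0.89 | 2.6% |
| 60% stable part, remainder decaying at 0.5 to 0.7 per quarter | 0.90 to 0.86 | 2.4% to 3.3% |
| First-order autoregressive, 0.7 to 0.95 per quarter | 0.86 to 0.80 | 3.3% to 4.6% |
| Falling SDs 1.4, 1.4, 1.3, 1.3 | 1.04 | 0.9% |

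**5. Practice effects that drift.** A simulation used 66 practices of 10 patients per arm, intra-class correlation 0.047, complete data and 2,000 runs.
- With constant patient-level variance and stable practice effects, the ratio was 1.02, which is 1 within Monte Carlo error of about 1.6%.
- With practice effects correlated 0.8 or 0.5 from one quarter to the next, it fell to 0.95 or 0.93 without any rise in variance.
- With drift and decaying patient correlation together, it was 0.83 to 0.75.

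**6. Family-wise error.** Four correlated changes from a common baseline were simulated, each tested at 1.25% with the pooled variance. Correlations between visits were taken to depend on lag as they do with baseline. In the main illustration the per-visit errors were 0.1%, 0.9%, 2.0% and 3.2%, and the chance of any false positive was 4.8%. Flatter decay gave 4.3%. Autoregressive patterns at 0.8 and 0.9 gave 5.1% and 5.3%.

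**The case against.** **The direction is not documented.** A reader might infer that the model makes the one-year standard error too small as a matter of fact. The article does not support that. It gives one SD of change and no correlations, so a rising variance is an expectation and not a stated input. With constant variance and stable practice effects the standard error is right, and with falling variance it is too large. This part of the objection stands, and the point is conditional for that reason.

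**The residual structure is not stated.** Random intercepts can be combined with visit-specific or correlated residuals, or with robust standard errors, and a condensed article may leave such details to the analysis plan. This is fair, and silence on the residuals is not itself the criticism. But the article does name the random intercepts as the device that handles the repeated measurements. Read in the ordinary way, that is a stated method with the consequence described.

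**The 5% control is not lost.** A reader might also infer that the trial's overall type I error is badly inflated. The calculation does not show this. The conservative early tests and the correlation between tests offset the excess at 12 months, and the family-wise error stays near 5%. Likewise, 9.2% describes an unadjusted 5% test or the non-coverage of a 95% interval. For the planned Bonferroni-adjusted test the figure is 3.2%.

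What survives is that the primary endpoint is the 12-month change. A preserved overall error rate does not repair that contrast's own interval and test.

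**Conclusion.** The point holds in conditional form. With ordinary independent residuals, the stated model imposes a common variance and correlation across visits. If the variance of HbA1c change rises over the year, the 12-month interval is too narrow and its test too liberal, while alpha moves from the early visits to month 12.

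In the decaying-correlation cases examined with stable practice effects, the 12-month standard error is about 5% to 20% too small, and the planned 1.25% test runs at about 1.8% to 4.6%. The main illustration gives 14% and 3.2%. These sizes rest on assumed correlations, complete data and, in the formula, the same variance pattern at patient and practice level.

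The sample size is unaffected. This is a cheap improvement, not an error that invalidates the plan.

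**What to change.** Either of two changes, fixed before outcome data are seen:

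1. Fit the four visits with an unstructured, or at least heterogeneous, within-patient covariance and a practice effect allowed to differ by visit. Prespecify a simpler structure to use if the model does not converge.
2. Keep the random-intercept model and base inference on practice-level robust standard errors with a small-sample correction.

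In both cases take the 12-month contrast from that model as the primary result.

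The cost is a sentence or two of wording and some code. The first option adds a few covariance parameters, affordable with 659 patients planned per arm, and may need the fallback. If the variance turns out constant and practice effects stable, little is lost.

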### Ethics

Before the start of study, we will present the physicians with an informed consent that outlines the EBMeDS intervention and the purpose of the trial to study the effectiveness of the system.

Individual informed consent from the patient cannot be sought. Reminders show up unexpectedly during practice when patient data deviate from evidence-based targets. It is not practical to ask for informed consent at these moments. Furthermore, reminding the physician of the informed consent forms at every consultation may bias the study results in favor of the intervention.

Data exports will be compliant with privacy legislation. Registration of the data processing to notify the Belgian Privacy Commission was performed on the commission website: http://www.privacycommission.be. Authorization for the use of medical and personal data was requested from the Sector Committee of Health.

Ethics committee approval for this study was obtained from the University Hospitals Leuven Medical Ethics Committee in May 2013.

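### HbA1c change is modelled without its baseline value, and covariates enter only if imbalance is shown; this gives away precision and leaves the primary model's covariates undecided until baseline data are compared

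*Protocol article*

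**What the plan says.** Under Primary and secondary outcomes: "Primary outcome is the one-year pre- to post-implementation change in HbA1c". The Sample size section is built on the same quantity, with an SD of HbA1c change of 1.3%.

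The Data analysis section says that "continuous outcome measures (change versus baseline in HbA1c, cholesterol levels, and blood pressure) will be assessed using linear mixed models", "with random intercepts for physician practices and random intercepts for patients to account for repeated measurements over time". It names no baseline value among the model terms.

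Covariates come in through a two-step rule. First: "Intervention and control groups will be compared regarding baseline variables to evaluate the randomization". Then: "If important differences in baseline characteristics are demonstrated between both groups, we will account for that by including the relevant variables in the model". The article does not say what makes a difference important, how it is demonstrated, or which variables are relevant. The composite scores follow the same pattern: "correction for imbalance in baseline characteristics will be applied if indicated".

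Baseline HbA1c, cholesterol and blood pressure are all on the list under Baseline measurements. The Randomization section describes simple randomization of practices and names no stratification.

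For the analysis of actual system use, similar models are fitted in the intervention arm only; "they will now include a measure for the use of EBMeDS as the main explanatory variable".

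**The concern.** There are two linked weaknesses.

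The first is precision. A change score subtracts the whole baseline value, whereas the follow-up value tracks baseline only in part. The rest of the baseline variation stays in the estimate as noise. Putting the baseline value in the model removes that noise, and here it would need no new data.

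The second is that the covariates of the primary model are not settled in advance. They depend on how the baseline comparison turns out and on a judgement that the article does not define. Two analysts could fit different primary models to the same data and both be following the text.

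The stakes are power that could be had for nothing, and a primary model that cannot be written down before the baseline data are seen.

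**Working it through.** **Inputs from the Sample size section.** Difference 0.3%; SD of change 1.3%; two-sided family-wise 5% with Bonferroni over four occasions, so 0.05/4 = 0.0125 per test; power 80%; withdrawal 10%; 10 patients per cluster; ICC 0.047.

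**The plan's own figure.** An exact two-sided t-test calculation gives 421 per arm. Withdrawal: 421 × 1.1 = 463.1, so 463. Design effect: 1 + (10 − 1) × 0.047 = 1.423. Then 463 × 1.423 = 658.8, so 659. Both stated figures reproduce.

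**Power as planned.** Effective patients per arm: 659 × 0.9 / 1.423 = 416.8. With SD 1.3, difference 0.3 and alpha 0.0125, power is 79.8%.

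**Power with baseline in the model.** Let s be the SD of HbA1c, equal at baseline and 12 months, and r their correlation.

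- Variance of change: 2(1 − r)s²
- Residual variance after baseline adjustment: (1 − r²)s²
- Ratio: (1 + r)/2

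The article gives neither r nor s, so r is an assumption shown as a range. The stated SD of change then fixes s = 1.3/√(2(1 − r)).

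| r (assumed) | implied s | variance ratio | adjusted SD | power at 416.8 per arm | 659 × ratio |
|---|---|---|---|---|---|
| 0.3 | 1.10 | 0.65 | 1.048 | 95% | 428 |
| 0.5 | 1.30 | 0.75 | 1.126 | 91% | 494 |
| 0.7 | 1.68 | 0.85 | 1.199 | 87% | 560 |
| 0.9 | 2.91 | 0.95 | 1.267 | 82% | 626 |

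The last column is the number per arm that would give the planned power with baseline in the model. The table also assumes the same r within and between practices, and the same ICC for the adjusted outcome.

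**Chance imbalance is the same loss.** Given a baseline difference D between arms, the unadjusted estimate shifts by (1 − r)D in absolute size. At r = 0.5, s = 1.3, and applying the same ICC to baseline values:

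- SD of D: 1.3 × √(2/416.8) = 0.090%
- SD of the shift: 0.5 × 0.090 = 0.045%
- SE of the change-score estimate: 1.3 × √(2/416.8) = 0.090%
- SE of the adjusted estimate: 0.090 × √0.75 = 0.078%
- Check: 0.078² + 0.045² = 0.0061 + 0.0020 = 0.0081 = 0.090²

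The shift accounts for exactly the excess variance, so the unadjusted standard error already contains it.

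**Does the conditional rule recover the loss?** The article gives no trigger, so p < 0.05 on baseline HbA1c was assumed. The simulation used cluster means, 66 practices per arm with 10 patients each, no withdrawal, alpha 0.0125 and 20,000 runs per setting.

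| r | change score only | adjust if p < 0.05 | always adjust | type I error of the conditional rule |
|---|---|---|---|---|
| 0.3 | 84% | 85% | 96% | 1.0% |
| 0.5 | 84% | 85% | 93% | 0.9% |
| 0.7 | 83% | 84% | 89% | 1.1% |

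Adjustment was triggered in about 5% of runs. Power is higher here than above because no withdrawal was applied.

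**The case against.** The outcome, the sample size and the model agree with one another: all use change, and the SD of 1.3% is that of change. On its own figures the trial has the power it claims. That stands; what is lost is an available gain.

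The covariates are chosen on baseline data, not on outcomes, and the Randomization section keeps data analysts blinded to allocation. This limits the room for choice but does not remove it, because the rule has no threshold and no list. A large HbA1c imbalance would presumably trigger adjustment. That also stands, but it leaves every smaller imbalance unadjusted. The simulated trigger is an assumption; a rule based on clinical size would behave differently.

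The threshold and the covariate list could sit in an analysis plan that is not shown. True, but the point is not that they are missing. The article states a conditional rule, and any threshold leaves it conditional. An analysis plan that always adjusts would contradict the article.

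A reader might infer that the primary estimate is biased or its type I error inflated. Neither is supported. Over repeated randomizations the unadjusted change score is unbiased, and the simulated conditional rule stayed below the nominal 1.25% for one covariate and a fixed trigger.

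A reader might also infer a spurious effect of system use. The Ethics section says: "Reminders show up unexpectedly during practice when patient data deviate from evidence-based targets". High HbA1c might then raise use and also fall further by regression to the mean. The documents do not carry the argument that far. Under Process evaluation, triggering is separate from use, since the physician must click to see the content, and use is logged at physician level. Reminders also cover all clinical areas, not only diabetes. The percentage of scripts opened is already planned as a measure.

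**Conclusion.** The point holds as a matter of precision and prespecification. The stated method is inferior to one that the collected data already allow. The gain from fixed baseline adjustment is positive for any r below 1 with equal SDs: from about 80% power to 91% at r = 0.5, 87% at r = 0.7 and 82% at r = 0.9. Its actual size depends on r, which the article does not give.

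It is not a finding of insufficient power, of bias under randomization or of excess false positives. The imbalance shift must not be counted as a second harm on top of the lost precision. For the use models, what can be said is limited: they compare patients within one arm, where randomization gives no protection, so baseline adjustment is sensible there too.

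The change should be made, but the trial remains valid without it.

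**What to change.** Replace the conditional sentence in Data analysis with: *The baseline value of the outcome is a fixed covariate in every model of a continuous outcome, whatever the observed balance.* Keep the baseline comparison as a descriptive table that triggers nothing.

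The primary outcome can stay as change in HbA1c. Once baseline is in a linear model, using change or the 12-month value as the response gives the same treatment effect. The sample size need not be altered.

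As a minor extension, carry the same baseline covariate into the exploratory use models in the intervention arm.

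The cost is one sentence. The baseline values are already collected.
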